#### Registered sick leave and RTW/entry in work or studies

Primary outcomes will be measured with registry data from MiDAS and SCB. MiDAS includes information about sick leave, extension and length, and previous sick leave periods. Full- or part-time is measured as sick leave on 25/50/75% or full-time (100%) and length. LISA includes information about income (salary, remuneration via the SPES or the municipality, reimbursement/grant for studies, remuneration via the SSIA). RTW/entry into work or studies is defined as any kind of activities such as: job training, traineeships or part or full-time employment with wages or benefits, or part or full-time studies. The analyses will be performed between- and within groups 12 months after inclusion, with the possibility of a follow-up at 24 months.

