The practice of RC’s has been developed and evaluated with positive outcomes [21, 25, 26] in the Swedish primary care. Nonetheless, to our knowledge, the effect of RC’s has not been investigated regarding reduced sick leave or RTW/entry in work or studies in patients with mental disorder within specialist psychiatric care.

This study protocol presents the design of a study aiming to evaluate a RC intervention for patients with mental disorder within the specialist psychiatry care. The objective of the study is to evaluate effects of a RC intervention on sick leave and RTW/entry in work or studies in patients with medium to severe affective and/or medium to severe anxiety disorders receiving treatment within specialist psychiatric care. The hypothesis is that the participants who receive the intervention will show a decrease in sick leave (extension and length) and to a higher degree have RTW/entry work or studies at 12-month follow-up, compared with participants receiving treatment as usual (TAU).

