### Participants and recruitments

The inclusion criteria are patients on sick leave, having moderate to severe affective and/or anxiety disorder (see Table 1 for ICD-codes), receiving treatment within a specialist psychiatric unit, aged 25–64 years, with or without employment. The exclusion criteria are multiple somatic illnesses, at high suicidal risk, fulltime sickness compensation (i.e. compensation for those between ages 30 and 64 who probably never will be able to work full time due to illness, injury or disability) [27], taking part in an ongoing vocational rehabilitation and being a patient outside of the county.

**Table 1 Tab1:** Diagnostic codes in accordance to the International Classification of Disease 10-SE

Disorder	ICD code
Bipolar disorder	F31.0-F31.9
Depression	F32.1-F32.3, F33.0-F33.4, F33.9
Post-traumatic stress disorder (PTSD)	F43.1
Generalized anxiety disorder	F41.1
Neuropsychiatric disorder	F84.0, F84.1, F84.4, F84.5, F90.0

The healthcare professionals within the healthcare unit can identify prospective participants for the study. Prospective participants can also be identified by the RC through a patient register called “Rehabstöd”, which is an IT-application showing all sick listed patients in the care unit. After consulting a doctor, potential participants, fulfilling the inclusion criteria and not the exclusion criteria, will be sent an invitation letter with information about the study. After 2 weeks, a research assistant will call the potential participant and provide verbal information about the study and invite him/her to participate. If the patient is interested in participating, a consent and baseline questionnaire will be mailed to the potential participant. Those willing to participate in the study must give their written consent and answer the baseline questionnaire. Thereafter, participants will be randomised to either the intervention or control group (see Fig. 1, Flow chart for recruitment process and datacollection). Randomisation will be achieved by using a computer generated list of random numbers and will not be stratified.

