#### Rehabilitation coordinator intervention

The RC meets the patients at the unit and assesses rehabilitation needs that are relevant for the ability to RTW/entry into work or studies, by interviewing the patient. By mapping the patient’s rehabilitation needs, a plan for the rehabilitation can be established, focusing on RTW/entry in work or studies. The RC constitutes a contact person for the participant, provides individualised support, and can initiate and coordinate contacts within- (healthcare professionals) and outside of healthcare (e.g. the SSIA, the SPES, the municipality, and the potential employer) needed for the RTW process. The RC intervention is estimated to last for approximately 1 year for patients randomised to the intervention group.

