### Outcome measures

The primary outcomes of the study is to evaluate effects of the RC intervention. We will analyse the difference between the intervention group and the controls in proportion of patients 1) on full- or part-time sick leave (extension) and time on sick leave (length) and 2) who RTW/entry into work or studies at 12 months.

Secondary outcomes are to perform analysis concerning workability, health outcomes and care consumption between the intervention group and the control group.

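### Read literally, the sick-leave primary outcomes improve when a participant moves from sick leave to sickness compensation during follow-up

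*Protocol article*

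**What the plan says.** The Outcome measures section makes the first primary outcome the between-group difference in the proportion of patients "on full- or part-time sick leave (extension) and time on sick leave (length"). The register section sets the scale: "Full- or part-time is measured as sick leave on 25/50/75% or full-time (100%) and length". The source is MiDAS, of which the article says "MiDAS includes information about sick leave, extension and length, and previous sick leave periods". The hypothesis at the end of the Background fixes the favourable direction: participants given the intervention "will show a decrease in sick leave (extension and length").

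Sickness compensation appears once, under Participants and recruitments. Patients must be on sick leave, and those on full-time sickness compensation are excluded. The benefit is explained there as "compensation for those between ages 30 and 64 who probably never will be able to work full time due to illness, injury or disability". The article therefore treats the two as different statuses at entry and says nothing about a change from one to the other afterwards.

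The other primary outcome, RTW/entry, "is defined as any kind of activities such as: job training, traineeships or part or full-time employment with wages or benefits", or studies. Income data come from a second register: "LISA includes information about income (salary, remuneration via the SPES or the municipality, reimbursement/grant for studies, remuneration via the SSIA"). No rule uses these data to interpret an exit from sick leave.

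**The concern.** A participant can leave sick leave by recovering work capacity or by being granted a longer-term benefit because that capacity is not expected to return in full. The stated outcome cannot tell the two apart. Both remove the participant from the proportion at 12 months, and both stop the count of days.

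Randomisation does not settle this, because the move happens after allocation and the intervention may influence it. The RC "can initiate and coordinate contacts within- (healthcare professionals) and outside of healthcare", and the SSIA is named among the outside parties. Intention-to-treat analysis keeps the participant in the assigned arm but leaves the outcome value as it is. Multiple imputation does not help either, because the status is recorded, not missing. The linear regression on length would take the shortened count at face value. A reported fall in sick leave could then be, in part, a change of benefit.

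**Working it through.** **The plan's own figure.** The Power calculation section gives 121 per group for a 15-point difference in RTW/entry, two-sided 5%, about 80% power. The control rate is not stated. The pooled two-proportion formula without continuity correction is

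n = [1.96·√(2·p̄(1−p̄)) + 0.8416·√(p₁(1−p₁) + p₂(1−p₂))]² / (p₁−p₂)².

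With an assumed 15% against 30% (p̄ = 0.225), n = 120.5, rounded up to 121. Power at 121 is 0.802. The figure reproduces. It belongs to RTW/entry and is unchanged by this point; only the 121 per arm is carried forward.

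**How a transfer enters outcome 1.** Let B be the true share still unfit for work at 12 months, equal in both arms, and let t be the share of each arm moved to sickness compensation and therefore no longer on sick leave. The observed proportion on sick leave is B − t, so the apparent benefit is

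(B − t_control) − (B − t_RC) = t_RC − t_control.

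Only the difference in transfers matters.

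**Chance of a significant result favouring the RC arm.** With n = 121, it is Φ[(d − 1.96·SE₀)/SE₁]. Here d is the apparent difference, SE₀ = √(2·p̄(1−p̄)/121) and SE₁ = √(p₁(1−p₁)/121 + p₂(1−p₂)/121). B and the transfer rates are assumptions; the documents give neither.

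| B | Transfers, control / RC | Observed on sick leave, control / RC | Apparent benefit | Chance of significance in favour |
|---|---|---|---|---|
| 70% | 5% / 5% | 65% / 65% | 0 | nominal, 0.025 |
| 70% | 5% / 10% | 65% / 60% | 5 points | 0.12 |
| 70% | 0% / 10% | 70% / 60% | 10 points | 0.37 |
| 50% | 5% / 10% | 45% / 40% | 5 points | 0.12 |
| 50% | 0% / 10% | 50% / 40% | 10 points | 0.35 |
| 85% | 5% / 10% | 80% / 75% | 5 points | 0.15 |
| 85% | 0% / 10% | 85% / 75% | 10 points | 0.49 |

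For the second row: SE₀ = 0.0622, SE₁ = 0.0622, (0.05 − 1.96 × 0.0622)/0.0622 = −1.16, and Φ(−1.16) = 0.12. If transfers are instead more common in the control arm, the same sizes apply against the RC arm. Counting transferred participants as still absent returns both arms to B, and the apparent difference is zero in every row.

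**Length.** Someone who would otherwise be on sick leave all year and transfers at month 6 loses about 180 counted days. A 5-point difference in such transfers moves the difference in means by 0.05 × 180 = 9 days.

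**The case against.** The strongest reply is that this is an inference from silence. The article never says that everyone off sick leave has improved. It does not describe how MiDAS codes sickness compensation, and the extraction may count it with sick leave. It is also a condensed account, and a full protocol or analysis plan may hold a rule. All of that stands, so a reader who infers that the protocol scores sickness compensation as a success goes further than the text does. What remains is that the article does fix the outcome by percentage, register and direction, and separates the two statuses at entry. Followed as written, that definition gives the wrong-way reading.

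Second, RTW/entry guards against a false conclusion. It requires work, training or studies, so sickness compensation alone does not qualify, and a change of benefit would show up as less sick leave with no gain in RTW. This is a real but partial safeguard, because sick leave is listed as a primary outcome in its own right and could be reported as a benefit by itself.

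Third, a reader might infer that the comparison is necessarily biased. It is not: equal transfers with equal true rates give no difference. The case for unequal transfers is only plausible. The RC may initiate outside contacts, but usual care can also include support for the patient's financial security.

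Fourth, two comparisons should be avoided. The 15-point design difference was set for RTW/entry and is no yardstick for sick leave. The eligibility text concerns full-time work at ages 30 to 64, so it does not make sickness compensation the worst vocational result, and it says nothing about participants aged 25 to 29.

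**Conclusion.** The point holds in a limited form. As defined in the article, the sick-leave outcomes move in the favourable direction when a participant transfers to sickness compensation, and no stated rule prevents it. The resulting bias equals the difference in transfer rates between arms, point for point. In the assumed range it is 0 to 10 points, with a chance of a significant result in favour of about 0.12 at 5 points and 0.37 at 10 points when B is 70%. The actual size within 12 months is unknown. The conclusion rests on two assumptions: that the MiDAS sick-leave measure excludes sickness compensation, and that transfers differ by arm. RTW/entry and the sample size are untouched. The definition should be settled before analysis.

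**What to change.** In the outcome definition, state that extent and length cover sick leave plus any sickness compensation granted after randomisation, at its percentage, with days continuing to accrue from the grant date. Because only full-time recipients are excluded at entry, the same sentence should say how part-time compensation already held at baseline is treated. Report the sick-leave-only version as a sensitivity analysis, and tabulate by arm where participants go when they leave sick leave.

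The cost is a sentence or two and one added register variable, with no burden on patients. There are two downsides. Grant dates and percentages must be confirmed in the SSIA extraction, because the article describes LISA only as income data. The outcome also becomes total health-related absence, not sick leave alone, and should be labelled so.

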### Power calculation

The estimation of sample size was based on an outcome measure with two possible outcomes: proportion of patients who RTW/entry work or studies (positive outcome) and proportion of patients that has not RTW/entry work or studies (negative/unchanged outcome). The statistical programme Stata 15.0 has been used to estimate the study’s strength (statistical power). The power estimation was based on a two-sided 5% significance level. In order to detect a difference at 15% between the groups in the main outcome with around 80% power, at least 121 individuals in the intervention and the control group are needed, respectively.

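### Return to work is defined without reference to status at entry, so eligible part-time sick-listed patients who already work or study can be scored positive with no change

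*Protocol article*

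**What the plan says.** All references are to the protocol article.

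- **Eligibility** (Participants and recruitments): "The inclusion criteria are patients on sick leave, having moderate to severe affective and/or anxiety disorder". Patients may be with or without employment, and no minimum degree of sick leave is set. The exclusions nearest to this point are full-time sickness compensation and ongoing vocational rehabilitation.
- **Degrees of sick leave** (Registered sick leave and RTW/entry in work or studies): "Full- or part-time is measured as sick leave on 25/50/75% or full-time (100%) and length".
- **Definition of the outcome** (same section): RTW/entry "is defined as any kind of activities such as: job training, traineeships or part or full-time employment with wages or benefits"; studying, whether part- or full-time, also counts. The section gives 12 months after inclusion as the time of analysis and requires no change from entry.
- **Sample size** (Power calculation): a two-category outcome, whose second category is the "proportion of patients that has not RTW/entry work or studies (negative/unchanged outcome"). The target is stated as: "In order to detect a difference at 15% between the groups in the main outcome with around 80% power". The number given for this target is "at least 121 individuals in the intervention and the control group are needed, respectively". The control-arm rate is not stated.
- **Analysis** (Data management and analysis): logistic regression adjusted for potential confounders, which are not named.

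**The concern.** Take an employed patient on 50% sick leave who works the other 50%. The inclusion criterion admits this patient and no listed exclusion removes them. The vocational rehabilitation exclusion may catch some people in job training or traineeships, but not those in ordinary part-time work or study. Part-time employment with wages is on the list of qualifying activities, so the patient meets the outcome definition on the day of randomisation. If nothing changes for a year, the outcome section scores a positive result and the Power calculation section, read literally, a negative one.

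Two things are at stake. Two analysts could code the same participant in opposite ways on the outcome that sizes the trial. And if the outcome section is applied as written, participants who are positive in both arms whatever the treatment raise the control rate and leave less room for a difference between the arms.

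**Working it through.** **Inputs from the protocol article:** two-sided 5% level, power about 80%, a difference of 15% (read as percentage points), 121 per arm. **Not given, hence assumed:** the control rate, and f, the share already active at entry who stay active to 12 months in both arms.

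**Step 1: reproduce 121.** Let d be the difference, p̄ the mean of the two rates, A = √(2p̄(1−p̄)) and B = √(pC(1−pC) + pI(1−pI)). The pooled-variance formula without continuity correction is

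n = (1.960·A + 0.842·B)² / d².

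At 15% versus 30%: A = √(2 × 0.225 × 0.775) = 0.5906 and B = √(0.1275 + 0.21) = 0.5809, so n = (1.1575 + 0.4889)² / 0.0225 = 120.5, rounded up to 121. By symmetry 70% versus 85% also gives 121. In a scan of control rates from 5% to 75% in steps of 5 points, only these two give exactly 121. The protocol does not say which pair, if either, was used, so both are carried forward.

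**Step 2: power at 121 per arm.** Power = Φ[(d√n − 1.960·A) / B], with √121 = 11. With f = 0 this is 80.2% for either pair.

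**Step 3: three scenarios.**

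Scenario 1 applies the 15 points only to participants inactive at entry, from 15% versus 30%. The rates become pC = f + (1−f) × 0.15 and pI = f + (1−f) × 0.30. Example at f = 10%: pC = 0.10 + 0.90 × 0.15 = 0.235; pI = 0.10 + 0.90 × 0.30 = 0.370; d = 0.135; A = 0.6496; B = 0.6426; power = Φ[(1.485 − 1.273) / 0.6426] = Φ(0.33) = 63%.

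Scenario 2 is the same model from 70% versus 85%.

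Scenario 3 keeps an overall difference of 15 points, so only the control rate rises, as in scenario 1.

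| f | Scenario 1: rates, power | Scenario 2: rates, power | Scenario 3: rates, power |
|---|---|---|---|
| 0% | 15.0 v 30.0%, 80% | 70.0 v 85.0%, 80% | 15.0 v 30.0%, 80% |
| 10% | 23.5 v 37.0%, 63% | 73.0 v 86.5%, 75% | 23.5 v 38.5%, 72% |
| 20% | 32.0 v 44.0%, 49% | 76.0 v 88.0%, 68% | 32.0 v 47.0%, 67% |
| 30% | 40.5 v 51.0%, 37% | 79.0 v 89.5%, 61% | 40.5 v 55.5%, 65% |

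In scenarios 1 and 2 the difference is (1−f) × 15 points: 13.5, 12.0 and 10.5. The number per arm for 80% power would be 181, 256 and 353 in scenario 1, and 149, 166 and 173 in scenario 3.

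One combination goes the other way. If an overall 15 points were kept from a 70% starting rate, the rates would move away from 50% (73% v 88% at f = 10%) and the same formula gives 84%. The loss is therefore not universal.

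**Step 4: what bounds f.** The Discussion estimates that about 50% of the unit's patients are unemployed, so participants already in part-time paid work are at most about half; part-time study could add some. Exclusion of ongoing vocational rehabilitation removes some of the overlap. Nothing in the document narrows f further.

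**The case against.** The best defence is linguistic. Return and entry are words of transition, and the outcome section can be read as listing the activities that count as its destination rather than as dropping the need for a change. The gloss on the negative category in the Power calculation section supports that intent. This stands as far as it goes: a reader might infer a flat contradiction, but the text is better called ambiguous on intent. The operative definition still does not mention status at entry, and it is the definition that will be coded.

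A reader might also infer that the trial is known to enrol people who already meet the outcome. The documents do not say so. It follows only from an unrestricted criterion together with the 25/50/75% categories, which are given for outcome measurement, not for eligibility. Moderate to severe illness in specialist care and about 50% unemployment suggest that the group may be small.

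Scenario 1 alone should not be quoted as the loss. It assumes the low starting pair, applies the 15 points only to inactive participants, lets every active participant stay active in both arms, and uses an unadjusted test. An effect of the intervention on keeping work would soften the loss. So could adjustment: if entry status were a covariate, power would be near that of the inactive subset alone, about 76/71/65% at 15% versus 30% (121 × (1−f) per arm). The plan names no covariates, so this is possible but not promised, and adjustment does not turn unchanged part-time work into a return.

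Two further inferences carry little weight. Chance imbalance in sick-leave degree under unstratified randomisation is not bias, and the test allows for it. The two-week gap between invitation letter and call does not show that status goes unchecked, since the baseline questionnaire is completed before randomisation.

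Finally, one may say that such coding belongs in the analysis plan. Detail may; but here the article itself states a definition that sits badly with its own sample-size section.

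**Conclusion.** The point holds as a defect in a definition, with a cost in power that cannot be fixed from the document. As written, unchanged part-time work or study can count as success in the outcome section and as failure in the Power calculation section, and no exclusion prevents the case from arising. That holds whatever f is.

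The size depends on f, on the control rate and on what the 15 points refers to. Across the three loss scenarios, power at 121 per arm lies between 63% and 75% at f = 10%, between 49% and 68% at f = 20%, and between 37% and 65% at f = 30%. The document does not support the stronger conclusion that the trial is underpowered by a known amount. This should be fixed, but it does not undermine the trial by itself.

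**What to change.** 1. In the outcome section, define RTW/entry relative to status at inclusion, so that unchanged part-time activity is not a positive outcome. For participants with no work or study at inclusion, any listed activity at 12 months counts. For those already active, use a lower MiDAS sick-leave extent at 12 months than at inclusion as the measure of increase. MiDAS extent is the practical choice because the protocol describes LISA as income information, from which a work or study share is not directly available.
2. Word the negative category in the Power calculation section to match.
3. Pre-specify sick-leave extent at randomisation, from MiDAS, as a covariate.
4. Report RTW/entry among those on 100% sick leave at inclusion as a sensitivity analysis.

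Settle this before outcome data are seen. The cost is a slightly more complex definition, with a different threshold for those already active and some overlap with the sick-leave extent outcome, plus one variable derived from register data already planned. No extra patients or visits are needed for the redefinition. The 121 per arm stands if the redefined outcome has rates of 15% versus 30%, or 70% versus 85%.

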### Background measure

#### Demographics

Information about educational level and country of birth and care of others (relatives or children) will be obtained through study specific questions.

#### Health related factors

Information on medical diagnosis will be collected from the patient record. General health is assessed with Self-reported health (SRH) measured with the single question ‘In general, how would you rate your health?’, answered on a five-point Likert scale from 1 = ‘Very good’ to 5 = ‘Very poor’ [29]. Health Related Quality of Life (HRQoL) is measured with the EQ-5D-3 L and includes following dimensions: mobility, personal care, anxiety/depression, everyday activities, pain/discomfort in 3 levels, where 1 = ‘No problems’, 2 = ‘Some problems’ and 3 = ‘Extreme problems’. EQ-5D-3 L also includes EQ visual analogue scale (EQ VAS), which measures self-rated health on a barometer graduated from 0 to 100 [30, 31]. The answers will be weighted and calculated to a score where 1 = full health and 0 = death. To measure pain, two questions will be used from the Örebro Musculoskeletal Pain Questionnaire [32]. The Hospital Anxiety and Depression Scale (HADS) will be used to assess anxiety and depression [33]. HADS is responded to on a four-point Likert scale from 0 to 3. The items are summed in two subscales, with scores ranging from 0 (no distress) to 21 (maximum distress). A score of 0–7 indicates a ‘non-case’, 8–10 a ‘possible case’ and 11–21 a ‘probable case’ of anxiety and depression. Psychological well-being is measured with the Questionnaire on well-being, consisting of 18 statements about how one feels feeling during the past week, answered on a five-point Likert scale from 1 = ‘Never’, 2 = ‘Rarely’, 3 = ‘Occasionally’, 4 = ‘Often and 5’ = ‘Very often’. Higher scores indicate a greater degree of perceived well-being [34]. Functioning in daily life will be assessed with the World Health Organization Disability Assessment Schedule (WHODAS) [35]. The General Self-Efficacy Scale (GSE) measures a person’s belief in their ability to handle various difficult demands in life [36]. GSE consists of 10 statements and is reported on a four-point Likert scale ranging from 1 = ‘Not at all true’ to 4 = ‘Completely true’. Consumption of care is measured through the individual question ‘Have you visited or been visited by any of the following in the last three months?’ with the following alternatives: doctor at hospital/health centre, district nurse, psychologist, social worker, physiotherapist, chiropractor/naprapath, etc., RC and been hospitalised. Answer options are: ‘No’, ‘Yes, once’, ‘Yes, several times’.

